No multiplicity adjustment for multiple comparison will be applied, given that statistical comparison will be performed only between the highest solnatide dose cohort and the placebo cohort. A statistical comparison between lower dose(s) and placebo will be performed only in case of statistical significance of the comparison between the highest solnatide dose cohort and the placebo cohort.

#### Days of hospitalization through day 28

Length of hospital stay (in days) is defined as the difference between the discharge date and the randomization date. Patients still in the hospital at day 28 or who die during hospitalization will be censored at day 28. Days of outpatient hospitalization will not be included. Summary descriptive statistics will be provided for the number of days of hospitalization.

#### Days of stay at ICU through day 28

Length of stay at ICU (in days) is defined as the number of calendar days a patient was in the ICU. Patients still in the ICU at day 28 or who die during the stay at ICU will be censored at day 28. Summary descriptive statistics will be provided for the number of days of stay at the ICU.
2.Safety analyses

Safety analyses will be conducted on the Safety Set and will be reported by actual treatment cohort. No methodology for missing data handling will be applied for safety parameters.

#### Drug-related adverse events through day 14

The incidence of treatment-emergent drug-related AEs through day 14 after randomization, both in terms of number of events and in terms of patients with at least one event, will be tabulated by MedDRA System Organ Class (SOC) and Preferred Term (PT).

#### All adverse events through day 28

According to the onset date of the event, AEs will be defined as follows:
Treatment-emergent AEs are those events with an onset date after treatment initiation;Non-treatment-emergent AEs are those events with an onset date between screening and treatment initiation.

Non-treatment-emergent adverse events will be listed only. The incidence of treatment-emergent adverse events (TEAE) will be tabulated by MedDRA System Organ Class (SOC) and Preferred Term (PT). The incidence of TEAEs will also be summarized by system organ class, preferred term, and severity (based on investigator’s judgment).

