The same analysis will be repeated for SAEs regardless of drug relationship, for drug-related SAEs, AEs with an outcome of death, and AEs leading to discontinuation of treatment. Deaths reportable as SAEs will be listed by patient and tabulated by MedDRA SOC and PT.

#### All-cause deaths through day 28

The number and proportion of deceased patients will be reported. In addition, the time (in days) from randomization to the event will be used for analysis. Subjects without an event will be censored at the earlier of the last contact date or day 28. The Kaplan-Meier estimates of the survival functions for each treatment cohort will be plotted and summarized.

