#### Serious adverse event reporting

Every SAE, regardless of suspected causality, occurring after screening and until at least 28 days after randomization must be reported to the sponsor within 24 h of site awareness. Any SAE experienced after this 28-day period should only be reported to the sponsor if the investigator suspects a causal relationship to the study treatment. Recurrent episodes, complications, or progression of the initial SAE must be reported as follow-up to the original episode within 24 h of the investigator receiving the follow-up information. Information about all SAEs will be recorded on the AE page of the eCRF and transmitted through the SAE tool. In case of technical difficulties, SAE notification can be carried out by sending a paper SAE form to the Pharmacovigilance Officer via email or by fax.

All SAEs still ongoing at end of study will be followed up by means of queries requesting updates. Other supporting documentation of the event may be requested by the study sponsor and should be provided as soon as possible. The study sponsor will be responsible for notifying Health Authorities of any unexpected fatal or life-threatening suspected adverse reaction as soon as possible, but in no case later than 7 calendar days after the sponsor’s initial receipt of the information.

Suspected unexpected serious adverse reactions (SUSARs) will be collected and reported to the competent authorities and relevant ethics committees in accordance with Directive 2001/20/EC or as per national regulatory requirements in participating countries.

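### Treatment-emergent status depends on onset date alone, so an event that starts between screening and first inhalation and then worsens on treatment stays out of the AE tables, and first-day events have no tie rule

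*Protocol article*

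**What the plan says.** The rule is in the protocol article, Statistical methods {20a}, under the heading on all adverse events through day 28. The classifier is the date: "According to the onset date of the event, AEs will be defined as follows". Two classes follow: "Treatment-emergent AEs are those events with an onset date after treatment initiation" and "Non-treatment-emergent AEs are those events with an onset date between screening and treatment initiation". The consequence for the second class is "Non-treatment-emergent adverse events will be listed only", while for the first "The incidence of treatment-emergent adverse events (TEAE) will be tabulated by MedDRA System Organ Class (SOC) and Preferred Term (PT") and again by severity.

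Other tables use the same filter. The drug-related table concerns "The incidence of treatment-emergent drug-related AEs through day 14 after randomization". After the main AE tables, "The same analysis will be repeated for SAEs regardless of drug relationship", and likewise for drug-related SAEs, AEs with a fatal outcome and AEs that lead to stopping treatment.

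Three other places bear on the rule:

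- Serious adverse event reporting, under {22}, collects "Every SAE, regardless of suspected causality, occurring after screening and until at least 28 days after randomization". It asks that recurrence, complications and progression of an SAE be filed as follow-up to the first report of it.
- Concomitant treatments, under {20a}, counts medication begun on the day treatment starts or later, and medication begun earlier that continues past that point.
- Criteria for discontinuing or modifying allocated interventions {11b} deals with clinically significant findings after enrolment, changes from baseline among them. It makes any new clinically relevant finding an AE.

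**The concern.** Outcomes {12} makes safety the main objective, and the DSMB section {21a} rests the final safety statement partly on the incidence of AEs and SAEs. The AE tables are therefore central output. A definition based on onset alone has two weak points.

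The first is worsening. If an event begins before the first inhalation and becomes more severe or serious after it, the change happened on treatment but the onset did not. The rule looks only at the onset.

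The second is the first dosing day. Dosing is twice daily, so that day contains the first exposure. A definition that says after, and speaks of dates, does not settle where an event with the same date as the first inhalation belongs.

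With 20 patients per active dose, one or two patients moved from a table to a listing would change the picture of a dose group.

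**Working it through.** No stated figure depends on this definition, so the check applies the rule to typical cases and then asks whether the effect can be sized.

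**Step 1. Apply the rule to four cases.**

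| Case | Onset relative to first inhalation | Class as written | Where it appears |
|---|---|---|---|
| A. New event on a later treatment day | After | Treatment-emergent | Tables |
| B. AE or SAE that starts after screening and before dosing, then worsens on treatment | Before | Non-treatment-emergent | Listing only |
| C. Event dated on the first dosing day, starting after the inhalation | Same date, later time | Depends on the reading | Tables or listing |
| D. Condition in the medical history that worsens on treatment | Depends on whether it becomes a new AE | Probably treatment-emergent | Probably tables |

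**Case B** follows directly from the text. Onset is the only criterion, and nothing gives worsening an onset of its own. For SAEs the reporting rule goes further, because progression is added to the existing report and so stays tied to the earlier onset. Such SAEs will be on record, since collection starts after screening.

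**Case C** has two readings. If initiation means the moment of the first inhalation and onset times are compared, the event is treatment-emergent. If calendar dates are compared, an equal date is not after, and the event falls to the listing. The definition does not choose. The safety analysis section also says that missing data will not be handled for safety parameters, so a same-day event without a time has no assigned place. The medication rule settles both matters left open here: it includes the start day, and it includes what began earlier and continued.

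**Case D** is different. Section {11b} treats changes from baseline after enrolment as findings to be assessed and makes new clinically relevant findings AEs. A worsening of baseline disease would then plausibly be entered as an AE with an on-treatment onset, and the rule would count it.

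**Step 2. Trace the reach.** Case B, and Case C on the date-only reading, are absent from the overall TEAE table, the severity table, the day-14 drug-related table, and the repeated tables for SAEs, drug-related SAEs, fatal AEs and AEs leading to discontinuation.

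**Step 3. Check what else would show them.** The listings contain them. All-cause deaths through day 28 are counted from randomization without this filter. Deaths reportable as SAEs are listed and tabulated with no treatment-emergent condition stated. Laboratory shift tables compare baseline with the worst value on treatment. Vital signs, ECG, hemodynamics and SOFA are summarized as change from baseline.

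**Step 4. Try to size it.** Case B needs the number of events that start between screening and first inhalation and the share that worsen. The article gives neither. Case C needs a first-day event rate, which is also not given. As an illustration only, let p be an assumed rate of patients with an event starting after dosing on the first day. In a dose group of 20 the expected number is 20p, and the chance of at least one is 1 − (1 − p)^20.

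| p (assumed) | Expected patients of 20 | Chance of at least one |
|---|---|---|
| 1% | 0.2 | 18% |
| 5% | 1 | 64% |
| 10% | 2 | 88% |
| 20% | 4 | 99% |

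For example, 1 − 0.95^20 = 0.64. The date-only reading tabulates none of these patients; comparison by date and time tabulates all of them. The table shows how much hangs on the unresolved tie. It does not estimate a loss.

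**The case against.** The strongest reply has three parts.

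First, initiation is an act, not a calendar day. In ordinary language a reaction to the first inhalation starts after initiation. This stands. A reader might infer that the rule definitely removes first-dose reactions, and might put the loss at 2 of 14 inhalations (14%), at 1 in 7 events of the treatment week or 1 in 28 through day 28, or at nearly all reactions to first exposure. The documents do not support those figures: they assume the date-only reading, and the fractions of events also assume evenly spread onsets. What remains is an ambiguity.

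Second, {11b} may already turn worsening of baseline disease into a new AE. This also stands. A reader might infer that worsening of pre-existing organ failure in general drops out of the tables, but the article does not say so. The reply does not reach an event already recorded as an AE or SAE before dosing, because its onset is fixed and, for an SAE, its progression is added to the same report.

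Third, handling of ties and missing times commonly belongs in the statistical analysis plan, which is not shown. That plan may refine the rule. The article does more than leave the matter open, however: it states a classifier, two classes and the consequence of each, and that stated rule is too narrow for Case B.

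**Conclusion.** The definition should be changed. The firm part is that an AE or SAE with onset between screening and first inhalation that worsens on treatment is kept out of all AE incidence tables using the treatment-emergent filter. This follows from the stated classifier, and the reporting rule reinforces it for SAEs. The weaker part is that events dated on the first dosing day could be excluded if only dates are compared; the text permits this but does not require it.

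The size cannot be computed from the article. The Case B share may be small: eligibility requires an ARDS diagnosis no older than 48 hours, which suggests a short interval before dosing, although the text does not state the time from screening to first inhalation. The events remain visible in listings, and deaths and laboratory worsening are reported separately. The issue is therefore incomplete AE tables, not vanished data. It matters because safety is the main objective and each active dose has only 20 patients.

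**What to change.** Replace the definition with one that has two limbs. A treatment-emergent AE is either:

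- an AE with onset at or after the start of the first inhalation, judged by date and time, where an event on the first dosing date with unknown time counts as treatment-emergent; or
- an AE with earlier onset that increases in severity or becomes serious after the first inhalation.

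Record the date of worsening for AEs and SAEs, and align the SAE follow-up rule so that progression filed under an existing report carries its own date. Use the one definition in every AE and SAE table.

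The cost is a sentence in the definition and one data item. For patients already enrolled, the worsening date may have to be taken from the site charts. A few first-day events that in fact preceded the dose will be counted, under the same rule in all arms. Sample size, power and alpha do not change.

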#### Vital signs

The absolute value and the change from baseline will be analyzed for each parameter (including heart rate, systolic and diastolic blood pressure and body temperature) by means of summary descriptive statistics at each time point through day 14 after randomization.

#### ECG parameters

Evaluation of ECG data will be performed by an external provider.

The absolute value and the change from baseline will be analyzed for each cardiac parameter (PQ, QRS, QT, and QTc intervals [Fridericia’s formula] and heart rate) by means of summary descriptive statistics at each time point (first 7 days of study). Based upon these parameters, heart rhythm anomalies / conduction abnormalities and changes/abnormalities in ECG morphology will be assessed and summarized.

#### Laboratory parameters

The absolute value and the change from baseline will be analyzed for each laboratory parameter (separately for hematology, clinical chemistry, blood gases, and urinalysis) by means of summary descriptive statistics at each time point through day 14. In addition, shift tables using the low/normal/high classification according to the laboratory normal ranges to compare baseline to the worst on-treatment value will be provided.

Listings of all laboratory data with values flagged to show the classifications relative to the laboratory normal ranges will also be generated.

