Mild	200 mmHg < P_aO2_/F_iO2_ ≤ 300 mmHg with PEEP or CPAP ≥ 5 cm H_2_O ^b, c^
Moderate	100 mmHg < P_aO2_/F_iO2_ ≤ 200 mmHg with PEEP ≥ 5 cm H_2_O
Severe	P_aO2_/F_iO2_ ≤ 100 mmHg with PEEP ≥ 5 cm H_2_O

Abbreviations: *CPAP*, continuous positive airway pressure; *F*_*iO2*_, fraction of inspired oxygen; *P*_*aO2*_, partial pressure of arterial oxygen; *PEEP*, positive end-expiratory pressure

^a^ Chest radiograph or computed tomography scan

^b^ If altitude is higher than 1000 m, the correction factor should be calculated as follows: [P_aO2_/F_iO2_ × (barometric pressure/760)]

^c^ This may be delivered noninvasively in the mild acute respiratory distress syndrome group

Most cases of ARDS in adults are associated with pulmonary sepsis (46%) or non-pulmonary sepsis (33%). Risk factors include those causing direct lung injury (e.g., pneumonia, inhalation injury, pulmonary contusion) and those causing indirect lung injury (e.g., non-pulmonary sepsis, burns, polytrauma, transfusion-related acute lung injury) [4].

ARDS is an orphan condition. The in-hospital mortality rate for ARDS is estimated to be between 34 and 55% [5]. Risk factors for mortality include older age, multiorgan dysfunction and presence of pulmonary and non-pulmonary comorbidities. Most ARDS-related deaths are due to multiorgan failure. Refractory hypoxemia accounts for only 16 percent of ARDS-related deaths [6].

Treatment of ARDS is supportive, including mechanical ventilation, prevention of stress ulcers and venous thromboembolism, nutritional support and treatment of the underlying disease. Pharmacologic options for the treatment of ARDS are limited. The use of corticosteroids is controversial; randomized controlled trials and cohort studies tend to support the early use of corticosteroids for decreasing the number of days on a ventilator; however, no consistent mortality benefit has been shown with this therapy [7, 8]. No targeted pharmacological treatment of patients with pulmonary permeability edema in ARDS is currently available, and therefore, new therapeutic approaches are warranted.

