##### Informed consent

Male or female ≥ 18 years of agePatient has been admitted to an ICU, is mechanically ventilated and stable in this condition for at least 8 h.Moderate-to-severe ARDS diagnosis as defined by the Berlin definition:
Onset of ARDS within 1 week of a known clinical insult or new or worsening respiratory symptoms.Bilateral opacities not fully explained by effusions, lobar/lung collapse, or nodules.Respiratory failure not fully explained by cardiac failure or fluid overload (origin of edema).PaO2/FiO2 ≤ 200 mm Hg with Positive End-Expiratory Pressure (PEEP) ≥ 5 cm H_2_O.
4.Verified ARDS diagnosis (moderate or severe according to Berlin definition) not older than 48 h.5.Extravascular lung water index (EVLWI) ≥ 10 ml/kg PBW as assessed with a validated bedside measurement (single indicator transpulmonary thermodilution measurement, such as with PiCCO® from Pulsion or VolumeView from Edwards).6.Patient who meets criteria for extensive hemodynamic monitoring as per international intensive care medicine standards.

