### Outcomes {12}

The main objective of this study is to investigate the safety of solnatide administration. Therefore, no formal primary and secondary outcomes are defined. Safety will be assessed by a review of mortality, incidence of adverse events, and serious adverse events, as well as by analysis of relevant laboratory data and ECG. The following parameters will be taken into account when assessing the safety of solnatide:
Vital signs (i.e., heart rate, systolic and diastolic blood pressure, and temperature)Clinical laboratory (i.e., white and red blood cell count, hematocrit, hemoglobin concentration, platelet count, creatinine, sodium, potassium, chloride, blood urea nitrogen, bilirubin, aspartate and alanine transaminases, lactate dehydrogenase, amylase, lipase, C-reactive protein, creatine kinase, arterial pH, PaO_2_, PaCO_2_, bicarbonate, SO_2_ as well as urine pH, specific weight, appearance, color, nitrites, proteins, glucose, urobilinogen, bilirubin, ketones, hematic pigments, and leukocytes)12-lead electrocardiogramHemodynamic parameters (i.e., mean arterial pressure, pulmonary blood volume, cardiac index, and cardiac outputNeed for vasoactive drugs24-h fluid balanceConcomitant medicationsAll-cause deathsUtilization of extracorporeal treatmentsAdverse events and serious adverse events

The secondary objective of this study is to evaluate possible endpoints for a future Phase III pivotal trial. Such endpoints investigated in this study include:
Extravascular lung water indexPulmonary vascular permeability indexMurray lung injury scoreOxygenation ratioVentilation parameters (i.e., plateau pressure, tidal volume, positive end-expiratory pressure, peak inspiratory pressure, respiratory rate, F_i_O_2_, mean airway pressure, peak airway pressure, ventilation mode)Lung complianceVentilation-free daysDays of ICUDays of hospitalizationDriving pressureSequential organ failure assessment

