## Data collection and management

### Plans for assessment and collection of outcomes {18a}

All data collected for this trial, e.g., eligibility criteria, demography, medical history, concomitant medication, physical examinations, vital sign measurements, laboratory results, and ECG data, is first recorded in site specific clinical charts based either on electronic or paper documents. If electronic charts are used, the electronic system should be compliant with applicable requirements. No study-related information will be stored on the eCRF only.

For laboratory tests, each site uses its own certified routine laboratory, which also provides its own reference values for each parameter obtained for study purposes. Measurements like ECG or hemodynamic parameters will be obtained using medical-grade, certified equipment.

Clinical scores are assessed based on the following resources:
Gas exchange, Organ failure, Cause, Associated disease (GOCA) score [26, 27]Sequential Organ Failure Assessment (SOFA) [28]Acute Physiology and Chronic Health Evaluation (APACHE) II score [29]Simplified Acute Physiology Score (SAPS) 3 [30, 31]

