## Statistical methods

### Statistical methods for primary and secondary outcomes {20a}

Data collected in this study will be listed and summarized as described below by treatment group. Data from all sites will be pooled and summarized. Continuous data will be summarized by mean, standard deviation (SD), median, first and third quartiles, minimum, and maximum. Categorical data will be presented by absolute and relative frequencies (n and %) or contingency tables. All statistical tables, listings, figures, and analyses will be performed by means of SAS® release 9.4 or later (SAS Institute, Inc., Cary, NC, USA).

A two-sided alpha level 0.05 will be considered. No alpha level adjustment will be made for secondary preliminary efficacy outcome variables and for multiple comparisons. Patients will be included in each analysis based on available assessments. No methodology for missing data handling will be applied, except for the EVLWI efficacy endpoint. Censoring rules for time-to-event analyses will be detailed in the Statistical Analysis Plan.

There is no primary efficacy endpoint as the primary objective of the study is to investigate the safety of solnatide. All efficacy analysis will be considered as secondary preliminary efficacy analyses. All secondary preliminary efficacy analyses will be performed based on the ITT set as primary analysis and on the PP set as supportive analysis and will be reported by planned treatment cohort.

No methodology for missing data handling will be applied for secondary preliminary efficacy endpoints, except for EVLWI. The homogeneity of treatment effects across different centers will not be tested.

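### Low/normal/high laboratory shift tables do not count patients who worsen markedly from an already abnormal baseline; adding graded and two-directional tables would close the gap

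*Protocol article*

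**What the plan says.** All of the text is in the protocol article.

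- **Role of laboratory data.** Section Outcomes {12} names laboratory results and the ECG among the inputs to the safety assessment: "Safety will be assessed by a review of mortality, incidence of adverse events, and serious adverse events, as well as by analysis of relevant laboratory". In the section on the data monitoring committee {21a}, laboratory data are part of the board's final statement on overall safety, which is the primary objective.
- **Shift tables.** Section Laboratory parameters: "shift tables using the low/normal/high classification according to the laboratory normal ranges to compare baseline to the worst on-treatment value will be provided".
- **Summaries.** The same section: "The absolute value and the change from baseline will be analyzed for each laboratory parameter", by descriptive statistics at each time point through day 14. Section {20a} fixes their content: "Continuous data will be summarized by mean, standard deviation (SD), median, first and third quartiles, minimum, and maximum".
- **Listings.** "Listings of all laboratory data with values flagged to show the classifications relative to the laboratory normal ranges will also be generated".
- **Reference ranges.** Section {18a}: "each site uses its own certified routine laboratory, which also provides its own reference values for each parameter".
- **Population.** Patients are ventilated in an ICU and must have "PaO2/FiO2 ≤ 200 mm Hg with Positive End-Expiratory Pressure (PEEP) ≥ 5 cm H_2_O". The background attributes most adult ARDS to pulmonary (46%) or non-pulmonary (33%) sepsis. Among the exclusion criteria, the only free-standing laboratory limit is a neutrophil count below 0.3 × 10^9/L. Lactate counts only together with low arterial pressure in septic shock. No renal, hepatic, platelet or CRP limit is listed.

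**The concern.** A three-class table works well when most patients start inside the normal range, because any important change then crosses a limit. It saturates when they do not. A patient who is high at baseline has no higher class to move to, and a patient who is low has no lower one. As an example, creatinine rising from 1.3 to 5 times the upper limit falls in the high-to-high cell, together with a patient whose creatinine did not change.

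The second weakness is the single worst value. Sodium, potassium, chloride, pH, PaCO2 and white cells can go wrong in either direction. If a patient has both a low and a high excursion, one value per patient shows one of them. Sodium and potassium are of some interest here because the drug acts on an epithelial sodium channel that the background section also places in the distal nephron. The same article reports very low systemic exposure.

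At stake is how easily a group-level signal can be read from laboratory data in a trial whose main objective is safety, with 20 patients per dose.

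**Working it through.** The protocol states no figure for this point, so there is none to reproduce. The check has two parts.

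**1. What each planned display shows for a patient already high at baseline who rises further**

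| Display | Shows the individual rise? | Counts such patients by cohort? |
|---|---|---|
| Shift table | No, the patient stays high-to-high | No |
| Change from baseline per time point | Yes if it is the most extreme, as the maximum (or minimum) | No |
| Listings | Yes, the values are there, but 1.3 and 5 times the limit carry the same flag | No |
| Adverse event tables | Yes, if the investigator reports the finding as an event | Yes, but as reported events, not from laboratory values |

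The gap is therefore in the last column: no laboratory summary counts these patients.

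**2. How many patients could be affected**

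Inputs:
- n = 20 per dose group (section Sample size {14}).
- b = share out of range at baseline, in the direction of concern, for a given analyte. The document gives no value. Assumed range: 20% to 80%.
- Illustration only: k = 4 patients in a group worsen seriously in that direction, independently of baseline class.

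Formulas: patients who cannot register further worsening = n × b; expected number of the k left in the same cell = k × b; probability that at least two are left there = 1 − (1 − b)^4 − 4b(1 − b)^3.

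| b | 20 × b | 4 × b | P(at least 2 of 4 in the same cell) |
|---|---|---|---|
| 20% | 4 | 0.8 | 0.181 |
| 40% | 8 | 1.6 | 0.525 |
| 60% | 12 | 2.4 | 0.821 |
| 80% | 16 | 3.2 | 0.973 |

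For b = 40%, the probability is 1 − 0.6^4 − 4 × 0.4 × 0.6^3 = 1 − 0.1296 − 0.3456 = 0.5248.

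The second column follows from the structure of the table once b is given. The last two columns also need the independence assumption, which the document can neither support nor refute. Within a randomized dosing step, b should be similar on solnatide and placebo, so the expected effect is a loss of sensitivity in both arms and not a tilt towards one of them.

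**The case against.** The strongest reply is that the shift table only supplements the rest. It is introduced as an addition to the summaries of level and change. Those summaries include quartiles, minimum and maximum, so a single large rise appears as the extreme change in its cohort. Complete listings give every value, and with 20 patients per dose they can be read. New clinically relevant findings are reported as adverse events, which are tabulated by cohort and severity, with serious events and events leading to discontinuation shown separately. SOFA is summarised to day 7. All of this stands.

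A reader might therefore infer too much: that the shift table is the only place where individual worsening can be seen, that only means and medians are reported, or that the monitoring board would be blind to such worsening. The documents support none of these readings. Nor do they call for a change to how PaO2 is shown, since the oxygenation ratio has its own summary.

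It can also be said that low/normal/high tables are conventional, that grading scales and the derivation of the worst value belong in the SAP, and that the article does not forbid separate low and high tables. The last is true: the text leaves the derivation open, and a SAP could define two values per analyte. But the three-class scheme is a stated method, not a detail left open, and it is poorly matched to this population. The sepsis percentages describe causes of ARDS in general and are not laboratory rates, so they support the direction of the argument and not its size.

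**Conclusion.** The point holds as a limited one. By construction, the planned shift table cannot register same-direction worsening in patients already out of range, and one worst value does not show both excursions of a two-directional analyte. For a given analyte this concerns 4 to 16 of 20 patients per dose if 20% to 80% start out of range. That share is an assumption. Abnormal baselines are inferred from the entry criteria and the scarcity of laboratory exclusions, and the inference is safest for blood gases and markers such as CRP.

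The consequence is that no planned laboratory summary counts patients per cohort who worsened markedly from an abnormal baseline, although laboratory data feed the main safety objective. The data themselves remain visible through the other displays, and nothing in the document shows that a board decision would change. This is a cheap improvement, not an error that invalidates the safety analysis.

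**What to change.** Keep the planned table and add the following in the SAP and table shells, with cut-offs fixed before unblinding:

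- Shifts from baseline to worst post-baseline value, by a standard toxicity grade or by multiples of the reference limit. Because ranges differ by site, multiples of each site's own limit put the values on a more comparable scale.
- For values abnormal at baseline, the worst multiple of the patient's own baseline, with counts per cohort.
- For two-directional analytes such as sodium, potassium and pH, one table for the lowest and one for the highest post-baseline value.

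Patients already in the top grade at baseline would still not move in the graded table, which is why the own-baseline multiple is useful beside it.

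The cost is a few more tables and their programming. The values and the site reference ranges are already collected, so no new data, visits or patients are needed.
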